### 5.5.4 Sub-group analysis

Subgroup analyses by vaccine type, age group and sex will be performed. We will consider conducting sub-group analysis by time-period too, especially if there is evidence of different circulating variants predominating.

### 5.5.5 Corrections for multiple testing

N/A

### 5.5.6 Sensitivity analysis

We will consider exploring the impact of alternative approaches to classifying the start of the exposed period (from day 0 of vaccination for both first and second doses, and day 21 after first dose), classifying COVID-19 hospitalisation on the basis of primary diagnosis (rather than any diagnostic position) and using a doubly robust estimator (i.e. including variables for confounder adjustment within regression models that already incorporate a propensity score).

### 5.5.7 Other analysis

We will consider conducting falsification analyses (negative controls) for alternative time periods (e.g. repeating analyses using time periods two months prior to first vaccination dose) to check the comparability of our exposure groups.

## 5.6 Pooled analysis

Results from the described analysis (Section 5.5) will be pooled across the UK nations. All nations should supply the following figures and tables.

5.6.1 Descriptive table of study population

Table of the characteristics of the underlying population (excluding elderly care home residents).

Code: 02_descriptive.R (lines 319-338)

| Characteristic | Level | Unvaccinated | | One dose ChAdOx1 | | Two doses  ChAdOx1 | | One dose BNT162b2 | | Two doses BNT162b2 | |
| --- | --- | --- | --- | --- | --- | --- | --- | --- | --- | --- | --- |
| Total | | | 1750310 | | 1767347 | | 862901 | |  | |  |
| Sex | Female | 803174 (45.9%) | | 532302 (61.7%) | | 911365 (51.6%) | |  | |  | |
|  | Male | 947136 (54.1%) | | 330599 (38.3%) | | 855982 (48.4%) | |  | |  | |
| Age (years) | Mean (SD) | 36 (13.7) | | 55.9 (16.4) | | 58.8 (15.3) | |  | |  | |
|  | Median (IQR) | 34 (16) | | 59 (24) | | 58 (20) | |  | |  | |
| Age group (years) | 18-64 | 1665366 (95.1%) | | 514525 (59.6%) | | 1203275 (68.1%) | |  | |  | |
|  | 65-79 | 52470 (3.0%) | | 324802 (37.6%) | | 379775 (21.5%) | |  | |  | |
|  | 80+ | 32474 (1.9%) | | 23574 (2.7%) | | 184297 (10.4%) | |  | |  | |
| Deprivation status † | 1 - High | 378104 (21.6%) | | 158081 (18.3%) | | 320872 (18.2%) | |  | |  | |
|  | 2 | 347560 (19.9%) | | 170138 (19.7%) | | 344723 (19.5%) | |  | |  | |
|  | 3 | 329048 (18.8%) | | 171937 (19.9%) | | 366204 (20.7%) | |  | |  | |
|  | 4 | 324051 (18.5%) | | 184204 (21.3%) | | 367064 (20.8%) | |  | |  | |
|  | 5-Low | 347067 (19.8%) | | 174089 (20.2%) | | 359778 (20.4%) | |  | |  | |
|  | Unknown | 24480 (1.4%) | | 4452 (0.5%) | | 8706 (0.5%) | |  | |  | |
| Urban/Rural index | 1 Large Urban Areas | 761350 (43.5%) | | 260620 (30.2%) | | 535334 (30.3%) | |  | |  | |
|  | 2 Other Urban Areas | 554621 (31.7%) | | 344947 (40.0%) | | 661485 (37.4%) | |  | |  | |
|  | 3 Accessible Small Towns | 139019 (7.9%) | | 84252 (9.8%) | | 180264 (10.2%) | |  | |  | |
|  | 4 Remote Small Towns | 67946 (3.9%) | | 43206 (5.0%) | | 99311 (5.6%) | |  | |  | |
|  | 5 Accessible Rural | 135931 (7.8%) | | 75302 (8.7%) | | 182029 (10.3%) | |  | |  | |
|  | 6 Remote Rural | 66964 (3.8%) | | 50122 (5.8%) | | 100218 (5.7%) | |  | |  | |
|  | Unknown | 24480 (1.4%) | | 4452 (0.5%) | | 8706 (0.5%) | |  | |  | |
| Number of risk groups ‡ | 0 | 1324630 (75.7%) | | 448039 (51.9%) | | 829753 (46.9%) | |  | |  | |
|  | 1 | 343193 (19.6%) | | 251725 (29.2%) | | 526054 (29.8%) | |  | |  | |
|  | 2 | 62186 (3.6%) | | 101524 (11.8%) | | 239430 (13.5%) | |  | |  | |
|  | 3 | 12733 (0.7%) | | 38518 (4.5%) | | 100966 (5.7%) | |  | |  | |
|  | 4 | 4420 (0.3%) | | 14699 (1.7%) | | 43167 (2.4%) | |  | |  | |
|  | 5+ | 3147 (0.2%) | | 8396 (1.0%) | | 27977 (1.6%) | |  | |  | |
| Number of previous tests § | 0 | 1467860 (83.9%) | | 643067 (74.5%) | | 1477853 (83.6%) | |  | |  | |
|  | 1 | 214044 (12.2%) | | 116474 (13.5%) | | 202719 (11.5%) | |  | |  | |
|  | 2 | 40341 (2.3%) | | 31064 (3.6%) | | 46050 (2.6%) | |  | |  | |
|  | 3 | 9947 (0.6%) | | 11717 (1.4%) | | 15097 (0.9%) | |  | |  | |
|  | 4-9 | 10719 (0.6%) | | 24158 (2.8%) | | 18650 (1.1%) | |  | |  | |
|  | 10+ | 7399 (0.4%) | | 36421 (4.2%) | | 6978 (0.4%) | |  | |  | |
| Average household age ¶ | Mean (SD) | 34.5 (13.9) | | 52 (18.2) | | 54.6 (17.8) | |  | |  | |
|  | Median (IQR) | 31.7 (16.25) | | 54.5 (31.5) | | 55.3 (27.25) | |  | |  | |
| Number of people in household ¶ | 1 | 542866 (31.0%) | | 272231 (31.5%) | | 620387 (35.1%) | |  | |  | |
|  | 2 | 385511 (22.0%) | | 309859 (35.9%) | | 608712 (34.4%) | |  | |  | |
|  | 3-5 | 727433 (41.6%) | | 262802 (30.5%) | | 505624 (28.6%) | |  | |  | |
|  | 6-10 | 81156 (4.6%) | | 16887 (2.0%) | | 30930 (1.8%) | |  | |  | |
|  | 11-30 | 6537 (0.4%) | | 850 (0.1%) | | 1301 (0.1%) | |  | |  | |
|  | 31-100 | 1655 (0.1%) | | 217 (0.0%) | | 222 (0.0%) | |  | |  | |
|  | 101+ | 5152 (0.3%) | | 55 (0.0%) | | 171 (0.0%) | |  | |  | |
| BMI | Underweight | 22839 (1.3%) | | 7172 (0.8%) | | 17856 (1.0%) | |  | |  | |
|  | Normal weight | 221423 (12.7%) | | 108021 (12.5%) | | 216994 (12.3%) | |  | |  | |
|  | Overweight | 1361930 (77.8%) | | 550521 (63.8%) | | 1126894 (63.8%) | |  | |  | |
|  | Obese | 144119 (8.2%) | | 197187 (22.9%) | | 405603 (22.9%) | |  | |  | |
| Smoking status | Ex-Smoker | 135461 (7.7%) | | 140896 (16.3%) | | 299894 (17.0%) | |  | |  | |
|  | Non-Smoker | 659177 (37.7%) | | 343925 (39.9%) | | 679009 (38.4%) | |  | |  | |
|  | Smoker | 283557 (16.2%) | | 200773 (23.3%) | | 436263 (24.7%) | |  | |  | |
|  | Unknown | 672115 (38.4%) | | 177307 (20.5%) | | 352181 (19.9%) | |  | |  | |
| Atrial fibrillation | | | 6268 (0.4%) | | 26750 (3.1%) | | 72957 (4.1%) | |  | |  |
| Asthma | | | 206703 (11.8%) | | 114308 (13.2%) | | 247126 (14.0%) | |  | |  |
| Blood cancer | | | 1811 (0.1%) | | 5358 (0.6%) | | 14739 (0.8%) | |  | |  |
| Heart failure | | | 3408 (0.2%) | | 11265 (1.3%) | | 33232 (1.9%) | |  | |  |
| Cerebral palsy | | | 622 (0.0%) | | 1036 (0.1%) | | 4356 (0.2%) | |  | |  |
| Coronary heart disease | | | 11998 (0.7%) | | 57178 (6.6%) | | 133101 (7.5%) | |  | |  |
| Cirrhosis | | | 3279 (0.2%) | | 6106 (0.7%) | | 14366 (0.8%) | |  | |  |
| Congenital heart disease | | | 3598 (0.2%) | | 10123 (1.2%) | | 24413 (1.4%) | |  | |  |
| COPD | | | 9734 (0.6%) | | 33608 (3.9%) | | 90563 (5.1%) | |  | |  |
| Dementia | | | 2350 (0.1%) | | 7411 (0.9%) | | 17478 (1.0%) | |  | |  |
| Diabetes type 1 | | | 2046 (0.1%) | | 5554 (0.6%) | | 14921 (0.8%) | |  | |  |
| Diabetes type 2 | | | 16798 (1.0%) | | 76948 (8.9%) | | 167878 (9.5%) | |  | |  |
| Epilepsy | | | 8910 (0.5%) | | 12308 (1.4%) | | 43449 (2.5%) | |  | |  |
| Fracture | | | 51152 (2.9%) | | 40527 (4.7%) | | 97860 (5.5%) | |  | |  |
| Neurological disorder | | | 1386 (0.1%) | | 4300 (0.5%) | | 12602 (0.7%) | |  | |  |
| Parkinson’s | | | 576 (0.0%) | | 2403 (0.3%) | | 6063 (0.3%) | |  | |  |
| Pulmonary hypertension | | | 724 (0.0%) | | 1596 (0.2%) | | 6510 (0.4%) | |  | |  |
| Pulmonary rare | | | 1436 (0.1%) | | 5635 (0.7%) | | 16043 (0.9%) | |  | |  |
| Peripheral vascular disease | | | 3373 (0.2%) | | 11786 (1.4%) | | 28862 (1.6%) | |  | |  |
| Rheumatoid arthritis or SLE | | | 3455 (0.2%) | | 12601 (1.5%) | | 31283 (1.8%) | |  | |  |
| Respiratory cancer | | | 1192 (0.1%) | | 2461 (0.3%) | | 7260 (0.4%) | |  | |  |
| Severe mental illness | | | 150214 (8.6%) | | 121762 (14.1%) | | 267033 (15.1%) | |  | |  |
| Sickle cell disease | | | 391 (0.0%) | | 763 (0.1%) | | 1904 (0.1%) | |  | |  |
| Stroke/TIA | | | 7729 (0.4%) | | 31281 (3.6%) | | 79952 (4.5%) | |  | |  |
| Thrombosis or pulmonary embolus | | | 7879 (0.5%) | | 17365 (2.0%) | | 50876 (2.9%) | |  | |  |
| Care housing category | Care home | 996 (0.1%) | | 4547 (0.5%) | | 2474 (0.1%) | |  | |  | |
|  | Homeless | 2221 (0.1%) | | 355 (0.0%) | | 1424 (0.1%) | |  | |  | |
| Learning disability or Down's | Learning disability | 22384 (1.3%) | | 9518 (1.1%) | | 34498 (2.0%) | |  | |  | |
|  | Down's | 113 (0.0%) | | 360 (0.0%) | | 1198 (0.1%) | |  | |  | |
| Kidney disease | CKD5 without dialysis or transplant | 7523 (0.4%) | | 37526 (4.3%) | | 103489 (5.9%) | |  | |  | |
|  | CKD5 with dialysis | 537 (0.0%) | | 1204 (0.1%) | | 4331 (0.2%) | |  | |  | |
|  | CKD with transplant | 383 (0.0%) | | 1211 (0.1%) | | 3103 (0.2%) | |  | |  | |
| * COVID-19 hospitalisation or death for vaccinated population after date of 1^st^ dose vaccination  † Deprivation status: Scottish Index of Multiple Deprivation (SIMD) 2020  ‡ Number of risk groups: Individual QCOVID risk groups found in Extended Table 11  § Number of previous tests: Proxy for working in a high-risk occupation (e.g. healthcare worker)  ¶ Household information taken from September 2020  + Care homes: All types of QCOVID care homes | | | | | | | | | | | |

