|  | Smoker | 632266 (24.6%) | 622361 (24.2%) | 205181 (24.6%) | 193166 (23.2%) | 427085 (24.5%) | 429195 (24.7%) |
|  | Unknown | 519876 (20.2%) | 519881 (20.2%) | 165482 (19.8%) | 171454 (20.6%) | 354394 (20.4%) | 348427 (20.0%) |
| BMI | Underweight | 25608 (1.0%) | 24269 (0.9%) | 8309 (1.0%) | 6869 (0.8%) | 17299 (1.0%) | 17400 (1.0%) |
|  | Normal weight | 317547 (12.3%) | 317567 (12.3%) | 107387 (12.9%) | 103954 (12.5%) | 210160 (12.1%) | 213613 (12.3%) |
|  | Overweight | 1653585 (64.2%) | 1649494 (64.1%) | 528838 (63.4%) | 533473 (64.0%) | 1124747 (64.6%) | 1116021 (64.1%) |
|  | Obese | 577134 (22.4%) | 582544 (22.6%) | 189185 (22.7%) | 189423 (22.7%) | 387949 (22.3%) | 393121 (22.6%) |
| Average household age ¶ | Mean (SD) | 53.8 (17.8) | 53.8 (18.0) | 52.4 (18.0) | 52.2 (18.2) | 54.5 (17.7) | 54.5 (17.8) |
|  | Median (IQR) | 55 (27.8) | 55 (28.5) | 55 (31) | 55 (31.6) | 55 (26.5) | 55 (27.2) |
| Number of people in household ¶ | 1 | 889811 (34.6%) | 876778 (34.1%) | 274915 (33.0%) | 265299 (31.8%) | 614896 (35.3%) | 611479 (35.1%) |
|  | 2 | 885516 (34.4%) | 899194 (34.9%) | 293331 (35.2%) | 300388 (36.0%) | 592185 (34.0%) | 598806 (34.4%) |
|  | 3-5 | 749050 (29.1%) | 749389 (29.1%) | 248351 (29.8%) | 251047 (30.1%) | 500699 (28.8%) | 498342 (28.6%) |
|  | 6-10 | 47116 (1.8%) | 46095 (1.8%) | 16063 (1.9%) | 15969 (1.9%) | 31053 (1.8%) | 30126 (1.7%) |
|  | 11-30 | 1763 (0.1%) | 1889 (0.1%) | 787 (0.1%) | 785 (0.1%) | 976 (0.1%) | 1104 (0.1%) |
|  | 31-100 | 387 (0.0%) | 379 (0.0%) | 164 (0.0%) | 193 (0.0%) | 223 (0.0%) | 186 (0.0%) |
|  | 101+ | 231 (0.0%) | 150 (0.0%) | 108 (0.0%) | 38 (0.0%) | 123 (0.0%) | 112 (0.0%) |
| * Rate calculated using person years as denominator  † Deprivation status: Scottish Index of Multiple Deprivation (SIMD) 2020  ‡ Number of risk groups: Individual QCovid risk groups found in Extended Table 11  § Number of previous tests: Proxy for working in a high-risk occupation (e.g. healthcare worker)  ¶ Household information taken from September 2020 | | | | | | | |

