## 5.7 Missing data

Missing data will be reported as percentages of total or raw numbers where possible. Previous analyses have demonstrated that little missing data exist for our key variables of interest. For covariates which may have a higher proportion of missing data (such as body mass index), we will either use records with no item missingness or use a missing category.

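### The BMI tables have no missing level and Overweight appears to absorb unrecorded values, so BMI is controlled only as coded in the match and the cohort regression

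*SAP*

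**What the plan says.** **The rule.** SAP 5.7 gives BMI as its example of a covariate with more missing data. For such covariates, "we will either use records with no item missingness or use a missing category".

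**Where BMI is used.** Section 5.3 lists BMI among the risk factors to be treated as confounders. Section 5.5.2 puts grouped BMI into the monthly propensity score models and judges the matching by covariate balance. The exact-match keys are propensity band, local authority and age, so BMI enters the match only through the score. Section 5.5.3 adjusts the whole-cohort Poisson models for risk factors, and that analysis carries the mortality outcome.

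**The tables.** In 5.6.1 the BMI block has four levels: "BMI | Underweight | 22839 (1.3%) | | 7172 (0.8%) | | 17856 (1.0", "Normal weight | 221423 (12.7%) | | 108021 (12.5%) | | 216994 (12.3", "Overweight | 1361930 (77.8%) | | 550521 (63.8%) | | 1126894 (63.8" and "Obese | 144119 (8.2%) | | 197187 (22.9%) | | 405603 (22.9". There is no Unknown row, although smoking, deprivation and urban/rural each have one. The matched table in 5.6.2 uses the same four levels; for both vaccines combined its Overweight row begins "Overweight | 1653585 (64.2%) | 1649494 (64.1".

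**The concern.** If BMI is often unrecorded, as 5.7 expects, the tables should show either a missing row or BMI counts that fall short of the column totals. They show neither, and one level is far larger than the others. Giving every person without a record a single typical value in the overweight range would produce this pattern.

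The Overweight level would then mix people known to be overweight with people of unknown BMI. Two consequences follow:

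- The balance check would compare a mixed category between arms. It could look good whatever the balance on true BMI.
- The cohort regression would adjust for a misclassified confounder, and the degree of misclassification could differ between vaccinated and unvaccinated people.

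Section 5.6 asks every nation to supply these tables and points to the code behind them. An unstated coding could therefore spread to all nations. Alternatively, nations that follow 5.7 would pool results adjusted for a differently defined BMI.

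**Working it through.** **1. Do the BMI rows fill the columns?** Inputs are the counts in 5.6.1 and 5.6.2. The Total row in 5.6.1 reads "Total | | | 1750310 | | 1767347 | | 862901". Its second and third entries are in the opposite order to the rows beneath, so vaccinated columns are identified here by their size.

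| Column | Underweight + normal + overweight + obese | Sum | Total |
|---|---|---|---|
| Unvaccinated | 22,839 + 221,423 + 1,361,930 + 144,119 | 1,750,311 | 1,750,310 |
| Vaccinated, smaller | 7,172 + 108,021 + 550,521 + 197,187 | 862,901 | 862,901 |
| Vaccinated, larger | 17,856 + 216,994 + 1,126,894 + 405,603 | 1,767,347 | 1,767,347 |
| Matched, unvaccinated | 25,608 + 317,547 + 1,653,585 + 577,134 | 2,573,874 | 2,573,874 |
| Matched, vaccinated | 24,269 + 317,567 + 1,649,494 + 582,544 | 2,573,874 | 2,573,874 |

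The sums are exact apart from an excess of one in the unvaccinated. The plan's percentages reproduce: 1,361,930/1,750,310 = 77.8%, and 63.8% in each vaccinated column.

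**2. Is the distribution credible as recorded data?** The age row reads "Mean (SD) | 36 (13.7) | | 55.9 (16.4) | | 58.8 (15.3", so the unvaccinated are about 20 years younger. They have the highest overweight share (77.8% v 63.8%) and the lowest obese share (8.2% v 22.9%).

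- Overweight:obese is 9.45 in the unvaccinated, against 2.79 and 2.78 in the vaccinated columns.
- Overweight:normal is 6.15, against 5.10 and 5.19.
- Smoking status is Unknown for 38.4% of the same unvaccinated people, and for 20.5% and 19.9% of the vaccinated. Complete BMI alongside that is hard to credit.

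**3. How large might the fill be?** The document gives no missing share. Assume that the true overweight:normal ratio r lies between 1 and 2 and is the same in each group. Then filled share = (overweight − r × normal)/total.

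| Column | r = 1 | r = 2 |
|---|---|---|
| Unvaccinated | (1,361,930 − 221,423)/1,750,310 = 65.2% | (1,361,930 − 442,846)/1,750,310 = 52.5% |
| Vaccinated, smaller | (550,521 − 108,021)/862,901 = 51.3% | (550,521 − 216,042)/862,901 = 38.8% |
| Vaccinated, larger | (1,126,894 − 216,994)/1,767,347 = 51.5% | (1,126,894 − 433,988)/1,767,347 = 39.2% |
| Matched, unvaccinated | (1,653,585 − 317,547)/2,573,874 = 51.9% | (1,653,585 − 635,094)/2,573,874 = 39.6% |
| Matched, vaccinated | (1,649,494 − 317,567)/2,573,874 = 51.7% | (1,649,494 − 635,134)/2,573,874 = 39.4% |

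Before matching the groups differ by about 13 to 14 percentage points. After matching the difference is about 0.2 points for both vaccines combined, and at most about 1.4 points within one vaccine.

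**4. Balance on BMI as coded.** SMD = (p1 − p2)/√[(p1(1 − p1) + p2(1 − p2))/2]. Before matching, vaccinated minus unvaccinated, it is −0.31 for overweight and +0.41 for obese. After matching, both vaccines combined, it is −0.005, 0.000, −0.003 and +0.005 for underweight, normal, overweight and obese. The largest by-vaccine value is 0.018 in absolute size.

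**The case against.** **The match.** A reader might infer that BMI is not controlled in the match at all. The documents do not support that. Grouped BMI is in the propensity model, underweight, normal and obese remain separate levels, and every matched SMD is below 0.02. On the assumption in step 3 the filled share is also nearly equal between matched arms. Smoking Unknown is 20.2% in both, which suggests, without proving it, that gaps in the GP record are similar. It follows that neither a lack of control in the match nor an imbalance in missingness after matching can be claimed.

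**The mechanism.** No section says that missing BMI was filled, and a mislabelled or merged level cannot be excluded in a table whose Total cells are already out of order. This stands, so the fill is an inference. The gap between the tables and 5.7 does not depend on it.

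**Other provisions.** Section 4.3 also allows closely related proxy variables when missingness is high. That does not cover an undeclared default category, and no proxy for BMI is named.

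**Status of the tables.** They look like one nation's example output: the deprivation footnote is Scottish, two columns are blank, and 5.6.2 gives 1,650,185 matched first-dose recipients in one place and 2,573,874 in another. The written rule in 5.7 is acceptable in itself. But these tables and their code are what all nations are asked to reproduce, so the coding behind them matters.

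**The assumed range.** At r = 1, obese people would make up 197,187/(862,901 − 442,500) = 46.9% of recorded BMI in the smaller vaccinated column, and overweight only 25.7%. The upper end of the range is therefore doubtful.

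**Conclusion.** The point holds in a limited form. Neither treatment in 5.7 is visible: there is no missing level, and the BMI counts account for everyone in the columns. Missing BMI coded as Overweight is a strong inference from the distribution, but the document does not state it.

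For the primary matched analysis, BMI is controlled as coded. The 64.2% v 64.1% in the 5.6.2 table cannot show balance on true BMI, so residual confounding by BMI is possible. For the unmatched cohort analysis, misclassification probably differs by vaccination status: about 53-65% of unvaccinated against 39-52% of vaccinated records filled, if r is 1 to 2 and common to the groups. Those columns count people, whereas 5.5.3 treats vaccination as time-varying and adjusts for age. The contrast in person-time, given age, may therefore be smaller.

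Neither the direction nor the size of any bias in the rate ratios can be derived from the document.

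**What to change.** 1. Confirm from the code how missing BMI was handled, and state it in 5.7. If nothing was filled, explain the Overweight share.
2. If values were filled, replace the fill with an explicit BMI-missing level, which 5.7 already permits. Use it in the propensity model, the cohort regression, the tables in 5.6.1 and 5.6.2 and the balance plot, identically in all nations.
3. Re-run the match and report the share with missing BMI by exposure group, before and after matching.

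A missing level does not recover true BMI for those without a record, but it makes missingness visible and lets balance on it be checked. The cost is a recode, a re-run of the match and dependent models, and one more row in each table.

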5.6.2 Descriptive table on matched cohort

Count of how many vaccine recipients were successfully matched, for first dose and second dose analyses.

Code: 03c_matching_ps_summary.R (lines 132-158) and

08c_matching_ps_summary.R (lines 347-393)

**First dose:**

| First dose vaccinated | Matched |
| --- | --- |
| 3,481,808 | 1,650,185 (47.4%) |

**Second dose:**

| Second dose vaccinated | Matched |
| --- | --- |
| 2,582,105 | 1,358,286 (52.6%) |

Population characteristics for vaccine controls and vaccine recipients by vaccine type in matched cohort analysis (excluding care home residents)

Code: 03c_matching_ps_summary.R (lines 102-169)

| **Characteristic** | **Level** | **Both vaccines** | | **BNT162b2** | | **ChAdOx1** | |
| --- | --- | --- | --- | --- | --- | --- | --- |
|  |  | **Unvaccinated** | **Vaccinated** | **Unvaccinated** | **Vaccinated** | **Unvaccinated** | **Vaccinated** |
| Total | | 2573874 | 2573874 | 833719 | 833719 | 1740155 | 1740155 |
| COVID-19 hospitalisation or death | All events, N (Rate per 1000*) | 2173 (8.9) | 1005 (4.1) | 840 (8.3) | 369 (3.7) | 1333 (9.2) | 636 (4.4) |
|  | Events 14 days+, N (Rate per 1000*) | 1029 (4.4) | 541 (2.3) | 488 (5) | 238 (2.4) | 541 (4) | 303 (2.2 |
| Sex | Female | 1418102 (55.1%) | 1403332 (54.5%) | 507290 (60.8%) | 508427 (61.0%) | 910812 (52.3%) | 894905 (51.4%) |
|  | Male | 1155772 (44.9%) | 1170542 (45.5%) | 326429 (39.2%) | 325292 (39.0%) | 829343 (47.7%) | 845250 (48.6%) |
| Age (years) | Mean (SD) | 57.9 (15.7) | 57.9 (15.7) | 56.1 (16.4) | 56.1 (16.4) | 58.8 (15.2) | 58.8 (15.2) |
|  | Median (IQR) | 58 (20) | 58 (20)` | 60 (23) | 60 (23) | 58 (19) | 58 (19) |
| Age group (years) | 18-64 | 1680152 (65.3%) | 1680152 (65.3%) | 491221 (58.9%) | 491221 (58.9%) | 1188931 (68.3%) | 1188931 (68.3%) |
|  | 65-79 | 691534 (26.9%) | 691534 (26.9%) | 319944 (38.4%) | 319944 (38.4%) | 371590 (21.4%) | 371590 (21.4%) |
|  | 80+ | 202188 (7.9%) | 202188 (7.9%) | 22554 (2.7%) | 22554 (2.7%) | 179634 (10.3%) | 179634 (10.3%) |
| Deprivation status † | 1 - High | 478638 (18.6%) | 468522 (18.2%) | 159802 (19.2%) | 152724 (18.3%) | 318836 (18.3%) | 315798 (18.1%) |
|  | 2 | 507601 (19.7%) | 503069 (19.5%) | 164176 (19.7%) | 163837 (19.7%) | 343425 (19.7%) | 339232 (19.5%) |
|  | 3 | 529350 (20.6%) | 525676 (20.4%) | 170884 (20.5%) | 165730 (19.9%) | 358466 (20.6%) | 359946 (20.7%) |
|  | 4 | 537544 (20.9%) | 539520 (21.0%) | 174078 (20.9%) | 178153 (21.4%) | 363466 (20.9%) | 361367 (20.8%) |
|  | 5 - Low | 508818 (19.8%) | 525164 (20.4%) | 160895 (19.3%) | 169391 (20.3%) | 347923 (20.0%) | 355773 (20.4%) |
|  | Unknown | 11923 (0.5%) | 11923 (0.5%) | 3884 (0.5%) | 3884 (0.5%) | 8039 (0.5%) | 8039 (0.5%) |
| Urban/Rural index | 1 Large Urban Areas | 783640 (30.4%) | 784728 (30.5%) | 258154 (31.0%) | 254808 (30.6%) | 525486 (30.2%) | 529920 (30.5%) |
|  | 2 Other Urban Areas | 971117 (37.7%) | 983172 (38.2%) | 318175 (38.2%) | 332206 (39.8%) | 652942 (37.5%) | 650966 (37.4%) |
|  | 3 Accessible Small Towns | 261494 (10.2%) | 259163 (10.1%) | 83271 (10.0%) | 81497 (9.8%) | 178223 (10.2%) | 177666 (10.2%) |
|  | 4 Remote Small Towns | 139935 (5.4%) | 137972 (5.4%) | 44273 (5.3%) | 40936 (4.9%) | 95662 (5.5%) | 97036 (5.6%) |
|  | 5 Accessible Rural | 259551 (10.1%) | 251953 (9.8%) | 76983 (9.2%) | 72623 (8.7%) | 182568 (10.5%) | 179330 (10.3%) |
|  | 6 Remote Rural | 146214 (5.7%) | 144963 (5.6%) | 48979 (5.9%) | 47765 (5.7%) | 97235 (5.6%) | 97198 (5.6%) |
|  | Unknown | 11923 (0.5%) | 11923 (0.5%) | 3884 (0.5%) | 3884 (0.5%) | 8039 (0.5%) | 8039 (0.5%) |
| Number of risk groups ‡ | 0 | 1243982 (48.3%) | 1255925 (48.8%) | 415784 (49.9%) | 432880 (51.9%) | 828198 (47.6%) | 823045 (47.3%) |
|  | 1 | 772262 (30.0%) | 763706 (29.7%) | 245304 (29.4%) | 243424 (29.2%) | 526958 (30.3%) | 520282 (29.9%) |
|  | 2 | 333638 (13.0%) | 330259 (12.8%) | 103715 (12.4%) | 98187 (11.8%) | 229923 (13.2%) | 232072 (13.3%) |
|  | 3 | 132252 (5.1%) | 133286 (5.2%) | 41209 (4.9%) | 37026 (4.4%) | 91043 (5.2%) | 96260 (5.5%) |
|  | 4 | 56040 (2.2%) | 55705 (2.2%) | 17117 (2.1%) | 14192 (1.7%) | 38923 (2.2%) | 41513 (2.4%) |
|  | 5+ | 35700 (1.4%) | 34993 (1.4%) | 10590 (1.3%) | 8010 (1.0%) | 25110 (1.4%) | 26983 (1.6%) |
| Number of previous tests § | 0 | 2105945 (81.8%) | 2100224 (81.6%) | 645635 (77.4%) | 637754 (76.5%) | 1460310 (83.9%) | 1462470 (84.0%) |
|  | 1 | 305290 (11.9%) | 311266 (12.1%) | 110764 (13.3%) | 114364 (13.7%) | 194526 (11.2%) | 196902 (11.3%) |
|  | 2 | 73485 (2.9%) | 73595 (2.9%) | 29242 (3.5%) | 29801 (3.6%) | 44243 (2.5%) | 43794 (2.5%) |
|  | 3 | 24995 (1.0%) | 24719 (1.0%) | 10565 (1.3%) | 10728 (1.3%) | 14430 (0.8%) | 13991 (0.8%) |
|  | 4-9 | 36566 (1.4%) | 36003 (1.4%) | 18077 (2.2%) | 18975 (2.3%) | 18489 (1.1%) | 17028 (1.0%) |
|  | 10+ | 27593 (1.1%) | 28067 (1.1%) | 19436 (2.3%) | 22097 (2.7%) | 8157 (0.5%) | 5970 (0.3%) |
| Smoking status | Ex-smoker | 427097 (16.6%) | 430664 (16.7%) | 135623 (16.3%) | 136623 (16.4%) | 291474 (16.7%) | 294041 (16.9%) |
|  | Non-smoker | 994635 (38.6%) | 1000968 (38.9%) | 327433 (39.3%) | 332476 (39.9%) | 667202 (38.3%) | 668492 (38.4%) |
|  | Smoker | 632266 (24.6%) | 622361 (24.2%) | 205181 (24.6%) | 193166 (23.2%) | 427085 (24.5%) | 429195 (24.7%) |
|  | Unknown | 519876 (20.2%) | 519881 (20.2%) | 165482 (19.8%) | 171454 (20.6%) | 354394 (20.4%) | 348427 (20.0%) |
| BMI | Underweight | 25608 (1.0%) | 24269 (0.9%) | 8309 (1.0%) | 6869 (0.8%) | 17299 (1.0%) | 17400 (1.0%) |
|  | Normal weight | 317547 (12.3%) | 317567 (12.3%) | 107387 (12.9%) | 103954 (12.5%) | 210160 (12.1%) | 213613 (12.3%) |
|  | Overweight | 1653585 (64.2%) | 1649494 (64.1%) | 528838 (63.4%) | 533473 (64.0%) | 1124747 (64.6%) | 1116021 (64.1%) |
|  | Obese | 577134 (22.4%) | 582544 (22.6%) | 189185 (22.7%) | 189423 (22.7%) | 387949 (22.3%) | 393121 (22.6%) |
| Average household age ¶ | Mean (SD) | 53.8 (17.8) | 53.8 (18.0) | 52.4 (18.0) | 52.2 (18.2) | 54.5 (17.7) | 54.5 (17.8) |
|  | Median (IQR) | 55 (27.8) | 55 (28.5) | 55 (31) | 55 (31.6) | 55 (26.5) | 55 (27.2) |
| Number of people in household ¶ | 1 | 889811 (34.6%) | 876778 (34.1%) | 274915 (33.0%) | 265299 (31.8%) | 614896 (35.3%) | 611479 (35.1%) |
|  | 2 | 885516 (34.4%) | 899194 (34.9%) | 293331 (35.2%) | 300388 (36.0%) | 592185 (34.0%) | 598806 (34.4%) |
|  | 3-5 | 749050 (29.1%) | 749389 (29.1%) | 248351 (29.8%) | 251047 (30.1%) | 500699 (28.8%) | 498342 (28.6%) |
|  | 6-10 | 47116 (1.8%) | 46095 (1.8%) | 16063 (1.9%) | 15969 (1.9%) | 31053 (1.8%) | 30126 (1.7%) |
|  | 11-30 | 1763 (0.1%) | 1889 (0.1%) | 787 (0.1%) | 785 (0.1%) | 976 (0.1%) | 1104 (0.1%) |
|  | 31-100 | 387 (0.0%) | 379 (0.0%) | 164 (0.0%) | 193 (0.0%) | 223 (0.0%) | 186 (0.0%) |
|  | 101+ | 231 (0.0%) | 150 (0.0%) | 108 (0.0%) | 38 (0.0%) | 123 (0.0%) | 112 (0.0%) |
| * Rate calculated using person years as denominator  † Deprivation status: Scottish Index of Multiple Deprivation (SIMD) 2020  ‡ Number of risk groups: Individual QCovid risk groups found in Extended Table 11  § Number of previous tests: Proxy for working in a high-risk occupation (e.g. healthcare worker)  ¶ Household information taken from September 2020 | | | | | | | |

